### Trial design {8}

The present study is designed as a superiority, double-blind, parallel-group, sham-controlled randomized clinical trial with an allocation ratio of 1:1. Study sites will include 4 University Hospital centers in France. In a 1 × 2 factorial design with sham, patients are randomized into two groups: active tDCS and sham tDCS. A total of 60 patients with schizophrenia will be randomly assigned to receive either active tDCS (*N*=30) or sham tDCS (*N*=30). Psychiatric and neuropsychological assessments will be performed at baseline (time of consent), at the end of the tDCS procedure, and at 1 and 3 months following the end of the tDCS procedure (maintenance effect). Auditory biomarker analyses will involve neurobiological measures (multimodal magnetic resonance imaging and neurophysiology) recorded at baseline and at 1 month after tDCS. Study schedule and study flowchart are presented in Figs. 1 and 2.

**Fig. 1 Fig1:**
[figure not shown]
Modelization of current strength pattern associated with the left fronto-temporal tDCS montage (red square: anode, blue square: cathode). **A** Whole brain. **B** Coronal view of the brain; cut through the auditory cortex

**Fig. 2 Fig2:**
[figure not shown]
Participant timeline

## Methods: Participants, interventions, and outcomes

### Study setting {9}

Participant recruitment will be conducted across four French centers:Centre Hospitalo Universitaire Grenoble Alpes, Department of Adult Psychiatry, Grenoble (10 participants). Neuroimaging platform: IRMaGE.Centre Hospitalier Alpes-Isère, Department of Psychiatry, Saint-Egrève (10 participants). Neuroimaging platform: IRMaGE.Centre Hospitalier Le Vinatier, Department of Psychiatry, Bron (20 participants). Neuroimaging platform: CERMEP.Centre Hospitalo-Universitaire de Saint-Etienne, Department of Psychiatry, Saint-Etienne (20 participants). Neuroimaging platform: IRMAS.

### Eligibility criteria {10}

The inclusion criteria include (1) subjects of both genders, diagnosed with recent-onset schizophrenia (first 3 years of illness), confirmed through the Structured Clinical Interview for the American Psychiatric Association Diagnostic and Statistical Manual of Mental Disorders, 5th edition (SCID-5); (2) aged 18–35 years; (3) intelligence quotient (IQ) > 55; (4) cognitive deficit confirmed by a MCCB total score *T*-score < 40; (5) the subjects should be receiving stable doses of antipsychotics for ≥ 4 weeks; and (6) the subjects are covered by a public health insurance.

The exclusion criteria include (1) pregnant (determined by urine pregnancy test in females of childbearing age) or breastfeeding women; (2) unstable or acute medical conditions; (3) subjects who receive involuntary treatment with no third party available, guardianship or protection of the court; (4) history of cranioencephalic trauma with loss of consciousness or central nervous system diseases that affect the brain; (5) current diagnosis of substance abuse or history of substance dependence in the last 6 months, except nicotine; and (6) MRI, PET or tDCS contraindications.

### Who will take informed consent? {26a}

Informed consent will be obtained by local investigators (psychiatrists) involved in the study. The investigator who obtains the consent will conduct clinical assessments throughout the clinical trial period. Patients will be truthfully and completely informed in comprehensible terms of the requirements, the objectives, the risks, and safety measures. They will be informed of their right to refuse to participate and to withdraw at any time without incurring any penalty or withholding of treatment on the part of her/his psychiatrist and of the investigator, if different. All of this information is described on an information/consent form that will be provided to the participant. Written consent of the participant will be collected by the investigator prior to final inclusion in the study.

### Additional consent provisions for collection and use of participant data and biological specimens {26b}

No additional consent provisions for collection and use of participant data and biological specimens are planned.

## Interventions

### Intervention description {11a}

tDCS (transcranial direct current stimulation subjects) is a noninvasive brain stimulation technique that involves the passage of a small electric current through the scalp and skull to modulate brain activity [10]. The study intervention consists of ten 20-min sessions of active or sham tDCS. Sessions will be delivered twice daily and separated by at least 2 h for 5 consecutive weekdays. The electric current will be generated by an electric stimulator (class IIa medical device). Systems from two commercial distributors are allowed in the study: NeuroConn GmbH ([name], Germany, [contact]; email: [name]) and Soterix 1x1 tDCS Stimulator (Model 1300A, [name], [contact]; email: [contact]).

The procedure for the subject’s installation and tDCS electrode placement will be standardized between study centers using specific training formation sessions. During the entire tDCS session, the subject is at “rest,” comfortably seated in a chair in a quiet room. The subjects will be asked to relax, keep their eyes open, and not perform any particular activity. A clinician will be present for the entire session duration. The current will be applied via a pair of rubber electrodes (7×5 cm, 35 cm^2^) placed on the surface of the scalp according to the international 10/10 system of EEG electrode placement. The anode will be placed equidistant from F3 and FP1 (AF3, left dorsolateral prefrontal cortex, Brodmann areas 8, 9, 10, and 46, depending on the subject). The cathode will be placed equidistant from I7 and P7 (TP7, left auditory cortex, Brodmann areas 22, 41, and 42, depending on the subject). The tDCS montage and current flow modeling are depicted in Fig. 1. The stimulation parameters will be set at 2 mA for 20 min, with a progressive increase during the first 30 s (ramp up) and a progressive decrease during the last 30 s (ramp down) of each session. The impedance of the applied current is monitored by the stimulator during each session. If the limit is exceeded (e.g., increase in impedance due to dryness or electrode drop), the stimulation automatically stops. The cut-off impedance is about 55 kΩ for a 2-mA stimulation. As a safety measure, the impedance will be systematically checked before the start of the stimulation. In case of impedance higher or equal to 55 kΩ, new electrodes will be used.

### Explanation for the choice of comparators {6b}

Sham stimulation is of critical importance in tDCS trials [30]. The sham procedure is developed by the tDCS device manufacturer, which allows using the same tDCS device and the same procedure (i.e., 10 sessions delivered during 5 consecutive weekdays) for both the active and sham procedures. Sham tDCS is based on mimicking typical sensations of active tDCS underneath the electrode site (e.g., itching, tingling). It consists in delivering an active stimulation for a few seconds to mimic these sensations and thus keep participants blind to the intervention. In the sham condition (20-min sessions), the electrodes will be placed in the same positions as in the active group; however, the stimulator will start with a 30-s ramp up, 40-s active stimulation, 18-min and 20-s sham stimulation (i.e., no current), and 30-s ramp down at the end of the stimulation.

### Criteria for discontinuing or modifying allocated interventions {11b}

Modification of the allocated intervention for a given participant (active tDCS or sham tDCS) based upon any reasons will not be allowed. In case of tDCS treatment discontinuation, the participant will be withdrawn from the study.

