### Provisions for post-trial care {30}

After inclusion, no simultaneous participation in other interventional clinical research will be authorized during the trial period. The evaluation of adverse reactions will be carried out for a duration of 3 months.

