#### Secondary outcome

##### Secondary outcome 2: clinical efficacy

Outcome 2a will be the number of responders at 3 months.

Outcome 2b will be the changes from baseline to 1-month and 3-month endpoints in each MCCB domains subscores (processing speed, attention/vigilance, working memory, verbal learning, visual learning, problem-solving, emotional awareness) and total score. To avoid learning effects, the MCCB will use different sets of parallel tests with the same difficulty levels at 1 month and 3 months.

Outcome 2c will be the changes from baseline to after tDCS and 1-month and 3-month endpoints in the following symptom measures:Schizophrenia symptoms will be assessed using the PANSS (Positive and Negative Syndrome Scale) total score. In addition, PANSS subscores for positive, negative, disorganization, depression, and grandiosity/excitement symptoms will be used as outcomes [32].Auditory hallucinations, one of the key symptoms of schizophrenia, will be assessed using the AHRS (Auditory Hallucination Rating Scale) [33].Negative symptoms will be additionally assessed using the Brief Negative Symptom Scale (BNSS) [34].Depressive symptoms will be assessed using the Calgary Depression Scale for Schizophrenia (CDSS) total score [30].Global symptom severity and treatment response will be assessed using the Clinical Global Impressions Scale (CGI) total score [35].Cognitive insight abilities will be assessed using the Beck Cognitive Insight Scale total score [36].Perceptual anomalies will be assessed using the self-rated Cardiff Anomalous Perceptions Scale (CAPS) total score [37].Subjective experience of negative symptoms will be assessed using the self-rated Self-evaluation of Negative Symptoms (SNS) total score [38].Subjective experiences of cognitive impairment will be assessed using the self-rated Subjective Scale To Investigate Cognition in Schizophrenia (SSTICS) total score [39].

Outcome 2d will be the changes from baseline to 1-month and 3-month endpoints in the following general outcome measures:Functional outcome will be assessed using the FROGS (Functional Remission Observatory Group in Schizophrenia) total score [40]Quality of life will be assessed by the Schizophrenia Quality of Life Questionnaire Short Form (S-QoL 18) total score [41]

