#### Clinical Global Impression (CGI)

The CGI is a brief 3-item clinician-rated scale that involves the assessment of the severity of the disorder at baseline (item 1), the assessment of overall improvement at follow-up (item 2), and the measurement of the therapeutic index which assesses the clinical efficacy and associated side effects (item 3) [35, 48].

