### Adverse event reporting and harms {22}

Safety assessment will be conducted according to the requirements of the MDR 2017/745 and MDCG 2020-10/1 statements (European commission) and article of the R1123-46 (French Public Health Code). The investigator will document in the CRF any adverse event observed of reported by the participant. The causal link with the use of the medical device (tDCS) will be assessed. Any adverse event will be monitored until it is completely resolved.

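### Stopping tDCS means leaving the study, so participants who stop lose the 1-month primary outcome and later contacts, which undercuts the planned intention-to-treat analysis

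*Protocol article*

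**What the plan says.** The rule is in the Protocol article, section {11b}: "In case of tDCS treatment discontinuation, the participant will be withdrawn from the study". It refers to the study, not only the treatment, and makes no distinction by reason.

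The Trial design section {8} places the assessments after baseline "at the end of the tDCS procedure, and at 1 and 3 months following the end of the tDCS procedure". The Intervention description {11a} gives ten sessions, two a day, over five consecutive weekdays. The primary outcome {12} is MCCB response at 1 month. Response at 3 months is a secondary outcome. The tolerance outcome, which includes the tDCS-AEQ, is taken after the last session.

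The Statistical analysis plan section promises both intention-to-treat and per-protocol analyses. Section {20c} defines the intention-to-treat set as randomised participants who have an assessment later than the ten-session treatment, and fills missing data by last observation carried forward.

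On safety, section {30} says: "The evaluation of adverse reactions will be carried out for a duration of 3 months". Section {22} adds: "The investigator will document in the CRF any adverse event observed of reported by the participant" and "Any adverse event will be monitored until it is completely resolved".

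**The concern.** Stopping a treatment and leaving a trial are different events. An intention-to-treat comparison needs the outcome of everyone randomised, including those who stopped. Section {11b} treats the two events as one, so the protocol itself creates missing primary outcomes in participants who may be willing to attend.

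These participants are unlikely to be a random subset. The unblinding section {17b} foresees clinical worsening serious enough to end the protocol for a participant, and serious adverse effects. It lists these as grounds for unblinding, but this shows that stopping for harm is expected. Two things are at stake: the primary comparison loses observations in a selected group, and the same group loses the scheduled contacts at which a new or late event could be noticed. A visit that is not held cannot be recovered at the analysis stage.

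**Working it through.** **1. Timing.** Treatment occupies five consecutive weekdays ({11a}). The later visits fall 1 and 3 months after the end of tDCS ({8}). Any stop during the course therefore precedes both visits.

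**2. Count.** Three assessments are scheduled after baseline: end of tDCS, 1 month and 3 months.
- Lost with certainty under {11b}: 2 of 3 (1 and 3 months).
- Possibly lost: the third (end of tDCS), depending on whether withdrawal takes effect before it is done. The text does not say.
- Trial total: 60 × 3 = 180 scheduled post-baseline assessments. If k participants stop, between 2k and 3k of these are lost. The document gives no value for k.

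**3. What those assessments carry.**
- End of tDCS: tDCS-AEQ and mood scale (the tolerance outcome), and symptom scales.
- 1 month: MCCB (the primary outcome), symptom, functioning and quality-of-life scales, and the repeat neurobiological measures.
- 3 months: MCCB (secondary responder outcome), and symptom, functioning and quality-of-life scales.

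**4. Other sections that might keep these participants in.** The retention section {18b} provides reminders and rebooking of missed visits, but grants no exception to {11b}. Section {20c} describes non-adherence through withdrawal date, visit number, reason and carried-forward outcomes, which fits withdrawal and not continued assessment. No section restores the visits.

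**5. Effect on the intention-to-treat analysis.** There are two possibilities under {20c}.
- If the definition is read literally, someone who stopped before session ten has no assessment after the full course and is outside the set. A randomised participant is then excluded.
- If the participant is kept and carried forward, the value used is the last MCCB available. The MCCB analysis times in {20a} are baseline, 1 month and 3 months, so that value is the baseline. The change is baseline − baseline = 0, which is below 0.5, so the participant is a non-responder by construction. The Trial design section and the Abstract can be read as also testing cognition at the end of treatment. If so, and if the participant attended, that score would be carried forward instead.

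Neither route uses an observed 1-month outcome.

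**6. Illustration of size.** First, the plan's own figure. Inputs from the Sample size section {14}: p1 = 0.33, p2 = 0.05, power 80%, significance level 0.05. Sidedness is not stated; two-sided reproduces the figure. With p̄ = 0.19:

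n = [1.96·√(2·0.19·0.81) + 0.8416·√(0.33·0.67 + 0.05·0.95)]² / 0.28²
= [1.087 + 0.436]² / 0.0784 ≈ 29.6, so 30 per arm and 60 in total, as stated. Power at 30 per arm is 0.805. The figure therefore contains no allowance for loss.

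Now assume that d of 30 in each arm have no 1-month MCCB. These values of d are assumptions. If these participants are excluded, n becomes 30 − d. If they are counted as non-responders, n stays at 30 and each rate is multiplied by (30 − d)/30.

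| d per arm | Power, excluded | Power, counted as non-responders |
|---|---|---|
| 0 | 0.805 | 0.805 |
| 1 | 0.791 | 0.787 |
| 2 | 0.777 | 0.769 |
| 3 | 0.761 | 0.749 |
| 4 | 0.744 | 0.728 |
| 5 | 0.727 | 0.707 |
| 6 | 0.708 | 0.685 |

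Both columns assume that those who remain respond at 33% and 5%. They show loss of information only and say nothing about bias.

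**The case against.** The strongest reply concerns safety. Three months of adverse-reaction evaluation are planned and are not limited to completers. Events observed or reported are documented and followed until they resolve. Participants are recruited through their regular clinic consultations ({15}), and trial data are checked against medical records ({19}), so leaving the trial does not end clinical contact. No section says that the three-month evaluation runs through the 1- and 3-month visits. This stands, and it narrows the safety part to lost scheduled opportunities to detect something new or late.

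A reader might go further and infer that safety follow-up ends for those who stop, or that {11b} contradicts {30}. The text supports neither: the two provisions can both be followed.

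A reader might also argue that a side-effect rating is lost at 1 and 3 months because one CGI item weighs efficacy against side effects. That is thin. The CGI is listed as a symptom outcome: "Global symptom severity and treatment response will be assessed using the Clinical Global Impressions Scale (CGI) total score". The dedicated tolerance instrument is the tDCS-AEQ, taken at the end of treatment.

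It can also be said that few people will stop a five-day course, and that an unseen analysis plan may refine the missing-data handling. The first may be true; the document gives no rate, although its Discussion names dropout as a limitation. The second does not help, because no analysis can supply visits that the protocol has cancelled. The rule in {11b} is stated outright and is not a detail left to another document.

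**Conclusion.** The point holds. Followed as written, {11b} costs each participant who stops two scheduled assessments for certain and possibly a third, including the 1-month primary outcome. It leaves that participant excluded from the intention-to-treat analysis or represented by a carried-forward value. It also removes scheduled contacts for detecting new or late adverse events, although known events are still followed.

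The total loss is 2k to 3k of 180 assessments for k participants who stop, with k unknown. The power figures are conditional on assumed losses. A reader might infer that the rule favours one arm. The documents give no stopping rates or reasons by arm, so no direction can be claimed. The conclusion rests on the plain wording of {11b} and on the five-day course preceding both follow-up visits. The rule should be changed; it does not invalidate the design.

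**What to change.** Amend {11b} so that stopping stimulation is recorded in its own right, with date, session number and reason, and is kept distinct from withdrawal from the study. State that participants who stop remain, unless they withdraw consent, in the end-of-tDCS, 1-month and 3-month assessments already scheduled, including the tDCS-AEQ, the MCCB and adverse-event collection. State that they are analysed in their randomised arm, and adjust the set definition in {20c} so that membership does not depend on having received all ten sessions. Retention for adverse events alone would not be enough, because the primary outcome would still be missing.

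The cost is an amended sentence in {11b}, a matching clause in {20c}, a record of stopping that mainly adds the session number (withdrawal date, visit number and reason are already planned), and at most the three visits already planned for each participant who stops. The decision on when stimulation should stop remains with the sponsor and investigators. The change does not guarantee 80% power, since people who stop receive less stimulation, but it replaces excluded or imputed values with observed ones.

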### Strategies to improve adherence to interventions {11c}

The 10 tDCS sessions will be delivered during the shortest possible interval allowed by safety standards (twice daily during 5 consecutive weekdays). In addition, research staff members will regularly contact the participants by phone to improve retention. These strategies may allow for reducing dropout rates and achieving the primary outcome of the study.

### Relevant concomitant care permitted or prohibited during the trial {11d}

No concomitant care is prohibited during the trial.

### Provisions for post-trial care {30}

After inclusion, no simultaneous participation in other interventional clinical research will be authorized during the trial period. The evaluation of adverse reactions will be carried out for a duration of 3 months.

### Outcomes {12}

All described instruments are validated in the French language.

#### Primary outcome

The primary outcome will be the number of responders at 1 month after tDCS, defined as the proportion of patients demonstrating a cognitive improvement greater than or equal to *Z*=0.5 from baseline on the MATRICS Consensus Cognitive Battery total score (MCCB). The MCCB is a gold-standard standardized test battery to assess cognitive functions in patients with schizophrenia [27, 28]. This criterion has been used and validated in both antipsychotic and cognitive remediation trials in schizophrenia [29, 31]. To avoid learning effects, the MCCB will use different sets of parallel tests with the same difficulty levels at baseline and 1-month.

#### Secondary outcome

##### Secondary outcome 2: clinical efficacy

Outcome 2a will be the number of responders at 3 months.

Outcome 2b will be the changes from baseline to 1-month and 3-month endpoints in each MCCB domains subscores (processing speed, attention/vigilance, working memory, verbal learning, visual learning, problem-solving, emotional awareness) and total score. To avoid learning effects, the MCCB will use different sets of parallel tests with the same difficulty levels at 1 month and 3 months.

Outcome 2c will be the changes from baseline to after tDCS and 1-month and 3-month endpoints in the following symptom measures:Schizophrenia symptoms will be assessed using the PANSS (Positive and Negative Syndrome Scale) total score. In addition, PANSS subscores for positive, negative, disorganization, depression, and grandiosity/excitement symptoms will be used as outcomes [32].Auditory hallucinations, one of the key symptoms of schizophrenia, will be assessed using the AHRS (Auditory Hallucination Rating Scale) [33].Negative symptoms will be additionally assessed using the Brief Negative Symptom Scale (BNSS) [34].Depressive symptoms will be assessed using the Calgary Depression Scale for Schizophrenia (CDSS) total score [30].Global symptom severity and treatment response will be assessed using the Clinical Global Impressions Scale (CGI) total score [35].Cognitive insight abilities will be assessed using the Beck Cognitive Insight Scale total score [36].Perceptual anomalies will be assessed using the self-rated Cardiff Anomalous Perceptions Scale (CAPS) total score [37].Subjective experience of negative symptoms will be assessed using the self-rated Self-evaluation of Negative Symptoms (SNS) total score [38].Subjective experiences of cognitive impairment will be assessed using the self-rated Subjective Scale To Investigate Cognition in Schizophrenia (SSTICS) total score [39].

Outcome 2d will be the changes from baseline to 1-month and 3-month endpoints in the following general outcome measures:Functional outcome will be assessed using the FROGS (Functional Remission Observatory Group in Schizophrenia) total score [40]Quality of life will be assessed by the Schizophrenia Quality of Life Questionnaire Short Form (S-QoL 18) total score [41]

